## Abstract

**Introduction::**

Triple-negative breast cancer (TNBC) is featured with the biological properties of strong aggressive behaviors, rapid disease progression, high risk of recurrence and metastasis, and low disease free survival. Patients with this tumor are insensitive to the endocrine therapy and target treatment for HER-2; therefore, chemotherapy is often used as routine treatment in clinical. Because of the fact that a considerable number of patients seek for Chinese herbal medicine (CHM) treatment after operation and chemotherapy and (or) radiotherapy, it is thus need to evaluate the correlation between Chinese herbal medicine treatment and prognosis.

**Methods and analysis::**

This is a multicenter, prospective cohort study started in March 2016 in Beijing. A simple of 220 participants diagnosed with TNBC were recruited from nine hospitals and are followed up every 3 to 6 months till March 2020. Detailed information of participants includes personal information, history of cancer, quality of life, symptoms of traditional Chinese medicine and fatigue status is taken face-to-face at baseline.

**Ethics and dissemination::**

The study has received ethical approval from the Research Ethical Committee of Beijing Hospital of Traditional Chinese Medicine affiliated to Capital Medical University (No.2016BL-014-01). Articles summarizing the primary results and ancillary analyses will be published in peer-reviewed journals.

**Trial registration::**

Chinese Clinical Trial Registry: ChiCTR-OOC-16008246.

## Introduction

1

Triple-negative breast cancer(TNBC) is defined by an immunohistochemical absence of expression for estrogen receptor (ER), progesterone receptor (PR), and human epidermal growth factor receptor-2 (HER-2),^[1]^ it accounts for about 10% to 15% of breast carcinomas.^[2]^ The disease shows the characteristic of highly invasive and malignant, prone to an early pattern of recurrence and metastasis.^[3]^ TNBC is a collection of different breast cancer that is still poorly characterized at molecular level, and lack of definitive prognostic markers and selective targets of therapy.^[4,5]^ At present, chemotherapy remains the predominant systemic treatment for TNBC patients in both the early and advanced-stages of the disease and data from many studies showing significant benefit of chemotherapy.^[6,7]^ There is no proven targeted therapies for TNBC and the patients are of poor prognosis. Based on the above reasons, TNBC becomes a hot spot in the research of breast cancer.

Traditional Chinese medicine (TCM) has a history of thousands of years and can adjust the body in balance to prevent the recurrence/metastasis of cancers.^[8]^ CHM based on TCM has been increasingly used over the past decades around the world and has become well known for its significant role in enhancing efficacy and reducing toxicity during chemotherapy,^[9]^ and also has a certain effect in preventing and treating cancer.^[10]^ It is estimated that the United States National Cancer Institute (NCI) spends around $120 million each year on TCM related research projects.^[11]^ TNBC patients and their caregivers often consider CHM as a therapeutic method besides operation and chemotherapy/radiotherapy. Relevant article^[12]^ reports that CHM plays an important role in the combined, consolidate and maintenance treatment of TNBC.

## Objectives

2

### Primary

2.1

The primary objective of this study is to explore the association of CHM and recurrence and metastasis rate.

### Secondary

2.2

1.To investigate the relationship between the Quality of life (QoL) and the use of CHM in patients with TNBC. We evaluated the QoL in TNCB patients with Functional Assessment of Cancer Therapy (FACT) Scale and Eastern Cooperative Oncology Group (ECOG) criterion.2.To evaluation the correlation between breast cancer related symptoms and the use of CHM. Breast cancer related symptoms include fatigue, sleep quality, depression, and anxiety.

## Methods and analysis

3

### Study design

3.1

This study is a multicenter, prospective cohort study. The study has started in March 2016 and is currently ongoing. Two hundred and twenty TNBC patients aged between 18 to 75 years with II-III stage after surgery are enrolled from 9 hospitals. All participants need to complete the standard chemotherapy and (or) radiotherapy specified by the National Comprehensive Cancer Network (NCCN) guidelines according to their disease states. At the time of the participants entered the study, the duration of the last chemotherapy and (or) radiotherapy was not more than half a year. The whole study consists of 2 stages, stage I comprises a cross-sectional study-baseline and stage II is a cohort follow-up study across a 3-year period. Participants will be followed up every 3 to 6 months till recurrence or metastasis for 3 years. The feasibility and preciseness of the whole process were supervised by 1 to 2 supervisors.

### Study settings and participants

3.2

The study is being performed in 9 hospitals in Beijing include Beijing traditional Chinese Medicine Hospital affiliate to Capital Medical University, China-Japan Friendship Hospital, People's Hospital of Peking University, Chinese PLA General Hospital, Cancer Hospital of Chinese Academy of Medical Science, Guang’Anmen Hospital of the China Academy of Traditional Chinese Medicine, Beijing Tiantan Hospital affiliate to Capital Medical University, Beijing Luhe Hospital affiliate to Capital Medical University, and Beijing Shijitan Hospital affiliate to Capital Medical University. All TNBC patients who came to the above hospitals should be screened. For those eligible patients, researchers will give her and her guardian the detailed description of this study. After obtained the informed consent of the patient and her family, she was enrolled in the study. Participants taking CHM in 1 of the above 9 hospitals were referred to as cohort 1 and patients received chemotherapy or radiotherapy without CHM belong to cohort 2. Doctors of traditional Chinese medicine in the above hospitals prescribe CHM for patients according to their clinical symptoms, tongue and pulse, doctors at the above nine hospitals will also provide life guidance for these TNBC patients. The study schema and estimated recruitment numbers are presented in Figure 1. Inclusion and Exclusion criteria are presented in Table 1. Two investigators will be responsible for the follow-up of each participant at baseline and every 3 to 6months, data collection schedule is presented in Table 2.

**Figure 1 F1:**
[figure not shown]
Project overview. TCM symptom^1^: qi deficiency, palpitation, dysphoria in chest and palms. ECOG-PS^2^: Eastern Cooperative Oncology Group Performance Status. RPFS^3^: Revised Piper Fatigue Scale. HADS^4^: Hospital Anxiety and Depression Scale. PSQI^5^: Pittsburgh sleep Quality Index. FACT-B Scale^6^: Functional Assessment of Cancer Therapy-B Scale. Safety assessment^7^: Computed Tomography/Brightness mode/Magnetic Resonance Imaging/Bone Scan, tumor markers (CEA, CA125, CA153), blood routine test, routine urine test, stool routine test, liver/kidney function, electrocardiogram. CRF = Case Report Form, TCM = traditional Chinese medicine.

**Table 1 T1:**
[figure not shown]
Inclusion/exclusion criteria.

**Table 2 T2:**
[figure not shown]
Data collection schedule.

### Ethical issues

3.3

The study registered in the Chinese clinical trial registry (No. ChiCTR-OOC-16008246) and received ethical approval from the Research Ethical Committee of Beijing Hospital of Traditional Chinese Medicine Affiliated to Capital Medical University (No.2016BL-014-01). Eligible patients participate in the study after obtained an informed consent.

### Outcomes

3.4

The primary outcomes measure are as follows:

#### Primary outcomes

3.4.1

The primary outcome of this study is 3-year disease-free survival and 3-year disease-free survival rate.

#### Secondary outcomes

3.4.2

1.To elucidate the correlation between the QoL and the use of CHM in patients with TNBC. We evaluated the QoL in TNCB patients with FACT Scale and ECOG criterion. FACT scale is a common form of a cancer treatment function evaluation system of the QoL in cancer patients developed by Cella et al.^[13]^ It is constituted by general version (FACT-G) for measuring the quality of life of cancer patients and specific scale in specific cancer. FACT-G consists of 27 entries and is divided into 4 quarters: these are physical well-being, social/family well-being, emotional well-being, and functional well-being. FACT-B adds the specific modules of breast cancer based on FACT-G. Each entry is set in a hierarchical setting (0–4), the higher the score, the better the quality of life. The ECOG criterion is developed by ECOG.^[13]^ The standardized criteria are highly detailed and used to evaluate the toxicity criteria, response criteria and definitions of response by organ site involvement. It is set to 0 to 5 score, the higher the score, the worse the physical condition.2.To evaluate the correlation between fatigue, sleep quality, depression, anxiety, and the use of CHM. Most TNBC patients exhibit symptoms associated with breast cancer such as fatigue, sleep disorders, depression, and anxiety. We selected Piper Fatigue Scale (PFS), Pittsburgh Sleep Quality Index (PSQI), and Hospital Anxiety and Depression Scale (HADS) to assess the extent of these symptoms. PSQI is a self-related questionnaire to evaluate the sleep quality in the past few months and is easy to understand and self rating.^[14]^ It consists of 19 self-assessments and 5 peer-assessments entries, scoring only 19 self-assessment questions. The total score ranges from 0 to 21, the higher the score, the worse the sleep quality. Fatigue is one of the frequently occurring symptoms in cancer patients,^[15]^ TNBC patients are no exception. Wu HS et al^[16]^ first use PFS in evaluating cancer-related fatigue(CRF). PFS includes 22 entries, respectively measuring from 4 aspects, such as behavior, seriousness, emotion, feeling and cognition, and sentiment. The 22 items are digital representation of 0 to 10, 0 indicates no and 10 indicates very serious. The higher the score, the heavier the tiredness. HADS was devised by Zigmond and Snaitha about 30 years ago,^[17]^ it is a simple and convenient clinical tool to analyze the subjective symptoms of patients. It consists of 14 items and each item sets 0 to 4 score, the higher the score, the severer the depression.

Each participant has a case report form and all relevant data will be recorded in it, 2 clinical research associates supervise the whole research process.

### Sample size calculation

3.5

The primary objective of the research is 3-year DFS rate and we use it as the basis for the calculation of sample size. Referring to the relevant large-scale cohort study,^[18]^ the 3-year DFS rate of TNBC patients after surgery is about 77%, we assume it to be increased to 86%^[19]^ with the treatment of CHM. The sample size calculation formula for cohort study is n = 2p(1-p)(uα + uβ)/(p1-p2),^[2]^ p = (p1 + p2)/2, α assign to 0.05 and β assign to 0.2, the power is 80%, we need 92 participants of each cohort. The drop-out rate is considered as 20%, then the sample size of each cohort is 110 and the total sample size is 220.

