### Statistical analysis

3.8

All statistical analysis will be performed using Statistical Packages of Social Sciences software (SPSS) 19.0. Statistical significance will be defined as the *P* < 0.05. Based on the data distribution, the measurement data will be analyzed by ANOVA or *U* Mann-Whitney test, counting data using *χ*^*2*^test or *U* Mann-Whitney test. The survival data will be analyzed by Kaplan-Meier method in 1, 2, 3-year DFS rate and the recurrence and metastasis rate, then draw the survival curve. The comparison of survival curves between the two cohorts is based on Log-rank method. Repeated ANOVA will be used to evaluate the repeated measures such as the QoL, physical condition, and symptoms related to breast cancer. Evaluation of therapeutic efficiency will be analyzed by the data of full analysis set (FAS) and per protocol set (PPS), safety evaluation will use the data of safety analysis set (SS) for statistical analysis.

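### The 92 per cohort comes from a formula with (uα + uβ) left unsquared; power for 77% versus 86% is about 35% (47% if one-sided), not 80%

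*Protocol article*

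**What the plan says.** Section 3.5 (Sample size calculation) takes the 3-year DFS rate as the basis for sizing, and Section 3.4.1 names it among the primary outcomes. The assumption is: "the 3-year DFS rate of TNBC patients after surgery is about 77%, we assume it to be increased to 86" per cent with Chinese herbal medicine. The formula is printed as "n = 2p(1-p)(uα + uβ)/(p1-p2"), followed by a comma and a superscript 2 set like a citation mark, with p as the mean of the two rates. The section then states: "α assign to 0.05 and β assign to 0.2, the power is 80%, we need 92 participants of each cohort". A 20% drop-out allowance raises this to 110 per cohort and 220 in total.

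Section 3.8 (Statistical analysis) sets significance at P < 0.05 without declaring a one-sided test, and says: "The comparison of survival curves between the two cohorts is based on Log-rank method".

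**The concern.** The usual formula for comparing two proportions squares the sum of the quantiles as well as the difference. Here the sum carries no square. For a 9-point difference between rates around 80%, 92 per group is far below what 80% power normally requires.

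If the square was lost only in typesetting, this is a cosmetic matter. If it was lost in the calculation, the study lacks its stated power on the outcome that sized it. Readers who trust the 80% would then take a non-significant comparison as reasonable evidence against a 9-point difference, when the study had little chance of detecting one.

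**Working it through.** **Inputs**, all from Section 3.5 unless noted:
- p1 = 0.77, p2 = 0.86, so the difference is 0.09 and its square is 0.0081
- p = (0.77 + 0.86)/2 = 0.815, so 2p(1−p) = 2 × 0.815 × 0.185 = 0.30155
- α = 0.05 (sidedness not stated) and β = 0.2, so uβ = 0.842
- uα = 1.645 one-sided or 1.960 two-sided
- uα + uβ = 2.486 one-sided or 2.802 two-sided; the squares are 6.183 and 7.849
- log-rank test at P < 0.05 (Section 3.8)

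**Step 1: reproduce the plan's figure.** The stray superscript 2 is read as the exponent on (p1−p2).

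| Formula | One-sided uα | Two-sided uα |
|---|---|---|
| 2p(1−p)(uα+uβ)/(p1−p2)², sum unsquared | 0.30155 × 2.486/0.0081 = **92.6** | 0.30155 × 2.802/0.0081 = 104.3 |
| 2p(1−p)(uα+uβ)²/(p1−p2)², standard | 0.30155 × 6.183/0.0081 = 230.2, so 231 | 0.30155 × 7.849/0.0081 = 292.2, so 293 |

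Only the unsquared, one-sided cell gives 92 (truncated). Other methods with the square in place do not come near it:
- continuity-corrected: 251 one-sided, 313 two-sided
- arcsine: 227 and 288
- log-rank by Schoenfeld: 222 and 281
- log-rank by Freedman: 232 and 297

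The one other near match is 91.3 with unpooled variance, and it too needs the unsquared sum and the one-sided quantile. Leaving the denominator unsquared gives between 8 and 26.

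**Step 2: power actually available for 77% versus 86%.** Power = Φ(0.09/√(0.30155/n) − uα). For n = 92, √(0.30155/92) = 0.05725 and 0.09/0.05725 = 1.572. Two-sided power is Φ(1.572 − 1.960) = 0.349, and one-sided power is Φ(1.572 − 1.645) = 0.471.

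| Evaluable per cohort | Two-sided | One-sided |
|---|---|---|
| 88 (110 less 20%) | 34% | 46% |
| 92 (as stated) | 35% | 47% |
| 110 (no loss) | 40% | 53% |

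The 88 row arises because 110 is 92 × 1.2 = 110.4. Allowing for 20% loss by division gives 92/0.8 = 115.

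**Step 3: does the log-rank test help?** Assume proportional hazards and full 3-year follow-up of all 92 per cohort.
- HR = ln 0.86/ln 0.77 = 0.577, and (ln HR)² = 0.5498² = 0.3023
- Events needed (Schoenfeld): 4 × 7.849/0.3023 = 104 two-sided, or 4 × 6.183/0.3023 = 82 one-sided
- Events expected: 92 × (0.23 + 0.14) = 34
- Power with 34 events: 36% two-sided, 48% one-sided; with 110 per cohort, 42% and 54%

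**Step 4: what 92 per cohort can show.**
- Detectable difference: for 77% versus 92%, p = 0.845, 2p(1−p) = 0.26195, and 0.26195 × 7.849/0.15² = 91.4. So 80% two-sided power exists for a difference of about 15 points.
- Precision: the 95% CI half-width for 77% versus 86% is 1.96 × √((0.77 × 0.23 + 0.86 × 0.14)/92) = 1.96 × 0.0569 = 0.111, about ±11 points. This is wider than the 9-point effect sought.

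**The case against.** **The exponents are visibly damaged in the printed formula**, so a missing square proves nothing by itself. That is right. The finding rests on the result: had the square been present in the calculation, the answer would have been about 231 or 293.

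**The one-sided quantile is an inference.** Section 3.5 gives only α = 0.05 and Section 3.8 only P < 0.05. This stands, and it means the 35% is the figure for a two-sided test, the usual reading of a log-rank or χ² test at P < 0.05. A one-sided 5% test would have 47% power and would miss the effect about half the time. Sidedness is the smaller part of the error: the lost square accounts for 92 against 231, and sidedness for 231 against 293.

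**The protocol is modest about its size.** Section 2.1 describes an exploratory aim. The Discussion says that the sample looks small, that time and funding limit it, and that follow-up will continue past three years, which would add events. These remarks soften the risk of an over-confident reading. They neither withdraw the 80% claim nor change power for the 3-year outcome on which the study was sized.

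**Conclusion.** The concern holds. With the plan's own inputs, 92 per cohort does not give 80% power for 77% versus 86% under either sidedness. Power is about 35% two-sided or 47% one-sided, and even 110 evaluable per cohort reaches only 40% or 53%. The planned 92 is under a third of the two-sided requirement (293) and about two-fifths of the one-sided one (231).

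That the square was missing from the calculation itself follows from reproducing 92. The one-sided uα is inferred in the same way. The log-rank figures additionally assume proportional hazards and complete 3-year follow-up. None of these assumptions, varied within reason, brings power near 80%. The power statement must be corrected.

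**What to change.** In Section 3.5:
- Print the formula with both squares, and state the sidedness. A two-sided test with uα = 1.96 is the natural reading of Section 3.8.
- State that the corrected formula gives 293 per cohort two-sided, so 92 is not its result. Present 220 as the number that time and funding allow, which the Discussion already concedes.
- Replace the 80% claim. With 92 evaluable per cohort, power is about 35% for 77% versus 86%, and 80% only for about 77% versus 92%. Add that 20% loss from 110 leaves 88, with about 34% power.

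In Section 3.8, state that the primary result will be reported as an effect estimate with its 95% confidence interval, and that P ≥ 0.05 will not be read as no association.

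The cost is wording in the protocol and any SAP, with no additional enrolment for this correction. The stated power becomes much less favourable.

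### With 20% drop-out, 110 per cohort leaves 88 evaluable, not the 92 the plan says it needs; 92/0.8 = 115 would be required

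*Protocol article*

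**What the plan says.** Section 3.5 (Sample size calculation) bases the sample size on the 3-year DFS rate, taken as 77% without Chinese herbal medicine and 86% with it. It sets "α assign to 0.05 and β assign to 0.2" and concludes "we need 92 participants of each cohort". It then makes the allowance for loss: "The drop-out rate is considered as 20%, then the sample size of each cohort is 110 and the total sample size is 220".

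The step from 92 to 110 is not written out. The total of 220 is repeated in the Abstract, in section 3.1 (Study design) and in section 4 (Discussion). None of these gives another drop-out rate or another basis for 110.

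**The concern.** A drop-out rate is a fraction of those enrolled. To have n patients left after a fraction d is lost, one must enrol n/(1 − d). Multiplying by (1 + d) always falls short, because the loss also applies to the patients who were added. The three printed figures (92 needed, 20% lost, 110 enrolled) look like the product of that multiplication.

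The allowance exists so that the number the calculation calls for is still there at the end of follow-up. The sample size rests on a 3-year rate compared as two proportions, so each patient lost before recurrence or three years reduces the count that the formula uses. The Discussion itself accepts that movement out of the cohorts cannot be avoided and that the sample looks small. The same slip would also carry over to any corrected base sample size.

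**Working it through.** **Inputs (all from section 3.5).** Needed per cohort: 92. Drop-out: 20%. Enrolled per cohort: 110; total 220. DFS rates: 77% and 86%. α = 0.05 with sidedness not stated, so both are shown. Power 80%.

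**1. Reproducing the plan's 110.**
- 92 × (1 + 0.20) = 110.4, rounded down to 110. This matches.
- 92/(1 − 0.20) = 115. This does not match.

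The multiplication is therefore inferred from the numbers. Step 2 does not depend on that inference.

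**2. What 110 delivers.**
- Left after 20% loss: 110 × 0.80 = 88, which is 92 − 88 = 4 short.
- Needed to keep 92: 92/0.80 = 115 per cohort, 230 in total, which is 5 per cohort and 10 overall above the plan.
- Largest loss at which 110 still leaves 92: 1 − 92/110 = 16.4%.

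**3. Effect on power.** Mean rate p = (0.77 + 0.86)/2 = 0.815, so 2p(1 − p) = 2 × 0.815 × 0.185 = 0.30155. The difference is 0.09. Power = Φ(0.09/√(0.30155/n) − u), with u = 1.960 two-sided or 1.645 one-sided.

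| Evaluable per cohort | 0.09/√(0.30155/n) | Power, two-sided | Power, one-sided |
|---|---|---|---|
| 92 | 1.572 | 34.9% | 47.1% |
| 88 | 1.537 | 33.6% | 45.7% |

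A calculation with separate variances for the two rates gives nearly the same two-sided values, 34.8% and 33.5%. With 115 fully evaluable, that calculation gives 41.9% two-sided and 54.5% one-sided.

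**4. Where 92 comes from.** The section prints "n = 2p(1-p)(uα + uβ)/(p1-p2),^[2]^ p = (p1 + p2)/2". If the bracketed 2 is read as the exponent of the denominator, and the sum of normal deviates is left unsquared as printed, one-sided α gives 0.30155 × (1.645 + 0.842)/0.0081 = 92.6. The standard formula squares that sum:
- one-sided: 0.30155 × (1.645 + 0.842)²/0.0081 = 230.2, so 231 per cohort;
- two-sided: 0.30155 × (1.960 + 0.842)²/0.0081 = 292.2, so 293 per cohort.

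This is a separate error. It matters here because the drop-out step would be applied to the corrected base as well:
- one-sided: 231/0.8 = 288.75, so 289 (231 × 1.2 = 277.2 would give 278);
- two-sided: 293/0.8 = 366.25, so 367 (293 × 1.2 = 351.6 would give 352).

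**5. Detectable difference at 88.** Hold the lower rate at 77% and solve 2p(1 − p)(u + 0.842)²/d² = 88, with p = 0.77 + d/2.
- Two-sided: d ≈ 0.152 (p = 0.8462; 0.2603 × 7.849/0.1524² ≈ 88).
- One-sided: d ≈ 0.138 (p = 0.8389; 0.2703 × 6.183/0.1378² ≈ 88).

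At 80% power, 88 per cohort can therefore detect about 77% versus 92% (two-sided) or 77% versus 91% (one-sided).

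**The case against.** The strongest reply is that the slip hardly matters. Four patients per cohort move power by about 1.3 points, and no design decision turns on that. This stands as a statement of size.

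A second reply is that 92 is not a valid 80%-power number in the first place, so restoring it protects nothing. This also stands. The drop-out error should be reported beside the formula error and ranked below it, and nobody should read 115 as a repair.

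Third, section 3.8 (Statistical analysis) plans Kaplan-Meier estimates and a log-rank comparison. There a patient lost to follow-up is censored and contributes time until loss, so counting only 88 overstates the information lost. This is right for the analysis and softens the practical effect. It does not reconcile section 3.5, whose formula counts patients with a known 3-year outcome and which itself applies a head-count allowance.

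Fourth, the Discussion says the size is limited by research period and funding. Section 3.5, however, presents 110 as the result of the calculation and not as a cap.

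None of these replies changes the arithmetic. The three figures are printed in the current text and disagree.

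**Conclusion.** The concern holds. Under the plan's own 20% drop-out rate, 110 per cohort yields 88 evaluable patients, 4 below its own requirement of 92. The correct enrolment for that requirement is 115 per cohort, 230 in total.

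The conclusion assumes only that drop-out means a fraction of those enrolled. How 110 was reached is an inference, and the conclusion does not rest on it. The power figures assume the two-proportion comparison of section 3.5. They are given for both sidednesses because the article does not state which applies. The effect on its own is small, but the sentence is wrong as written and should be corrected.

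**What to change.** Replace the drop-out step with n/(1 − 0.20). For the printed 92 this gives 115 per cohort and 230 in total. If the base number is corrected first, divide the corrected number by 0.8 in the same way.

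If 220 is fixed by period and funding, keep it and say what it delivers: 110 enrolled per cohort leaves 88 evaluable at 20% loss, or 92 if loss stays at or below 16.4%. State the sidedness of α, and give the power for 77% versus 86% at 88 (33.6% two-sided, 45.7% one-sided) or the difference detectable with 80% power (about 15 points two-sided, 14 points one-sided).

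The cost is a sentence or two of text and no extra enrolment. Correcting the head count alone makes the statement only slightly less favourable. Quoting power at 88 replaces the printed 80% with a much lower figure. Nearly all of that drop belongs to the formula error, and the text should say so.
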